## Abstract

**Background:**

Although surveillance data are limited in the US Affiliated Pacific, Alaska, and Hawaii, existing data suggest that the prevalence of childhood obesity is similar to or in excess of other minority groups in the contiguous US. Strategies for addressing the childhood obesity epidemic in the region support the use of community-based, environmentally targeted interventions. The Children’s Healthy Living Program is a partnership formed across institutions in the US Affiliated Pacific, Alaska, and Hawaii to design a community randomized environmental intervention trial and a prevalence survey to address childhood obesity in the region through affecting the food and physical activity environment.

**Methods/Design:**

The Children’s Healthy Living Program community randomized trial is an environmental intervention trial in four matched-pair communities in American Samoa, the Commonwealth of the Northern Mariana Islands, Guam, and Hawaii and two matched-pair communities in Alaska. A cross-sectional sample of children (goal n = 180) in each of the intervention trial communities is being assessed for outcomes at baseline and at 24 months (18 months post-intervention). In addition to the collection of the participant-based measures of anthropometry, diet, physical activity, sleep and acanthosis nigricans, community assessments are also being conducted in intervention trial communities. The Freely Associated States of Micronesia (Federated States of Micronesia, and Republics of Marshall Islands and Palau) is only conducting elements of the Children’s Healthy Living Program sampling framework and similar measurements to provide prevalence data. In addition, anthropometry information will be collected for two additional communities in each of the 5 intervention jurisdictions to be included in the prevalence survey. The effectiveness of the environmental intervention trial is being assessed based on the RE-AIM (reach, effectiveness, adoption, implementation, maintenance) framework.

**Discussion:**

The Children’s Healthy Living Program environmental trial is designed to focus on capacity building and to maximize the likelihood of sustainable impact on childhood obesity-related behaviors and outcomes. The multiple measures at the individual, community, and environment levels are designed to maximize the likelihood of detecting change. This approach enhances the likelihood for identifying and promoting the best methods to promote health and well-being of the children in the underserved US Affiliated Pacific Region.

**Trial registration:**

NIH clinical trial # NCT01881373

## Background

### Epidemiology of child obesity

Global prevalence estimates indicate that in 2004 approximately 10% (150-160 million) of school-aged children (5 to 17 years) were overweight, and 2-3% (35-40 million) were obese [1]. In the United States (US), the prevalence of obesity alone was estimated at 17% among 5 to 19 year-olds in 2009-2010 [2]. However, adequate prevalence data are lacking on overweight and obesity in the Pacific Region.

The health and social consequences of excess weight are substantial, and obese and overweight children are at risk for serious chronic illnesses. For example, being overweight and obese is a major risk factor for type 2 diabetes in children [3,4]. Obese children are also more likely than their peers to experience negative social and psychological consequences including discrimination, stigmatization, and low self-esteem [5-8].

Most researchers use body mass index (BMI) to measure child overweight and obesity; however, the BMI levels defining overweight and obesity may differ across countries depending on the reference data and cutpoints used [9]. Global estimates are often based on the World Health Organization cutpoints, which define overweight as > 1SD and obesity as > 2SD above the average (M) where M and SD are derived from a reference population for 5 to 19 year-olds, using data sets compiled by WHO [10,11]. In the US, in children aged 2 to 19 years, overweight is usually defined as greater than or equal to the 85^th^ percentile but less than the 95^th^ percentile and obesity as greater than or equal to the 95^th^ percentile, according to the BMI-for-age Centers for Disease Control and Prevention (CDC) growth charts [12].

### Prevalence of obesity in the US affiliated pacific region

Data from the National Health and Nutrition Examination Survey (NHANES), a program of studies designed to assess the health and nutrition status of adults and children in the US, are used to monitor the trends in child overweight and obesity [13]. The NHANES program, however, does not include data from the noncontiguous US states of Alaska and Hawaii or the US Affiliated Pacific Island Jurisdictions of American Samoa (AS), Commonwealth of the Northern Marianas Islands (CNMI), Guam, the Federated States of Micronesia (FSM), the Republic of Palau, and the Republic of the Marshall Islands (RMI) [14]. According to the few data sources available for the Pacific, the prevalence of child overweight and obesity combined (≥85^th^ percentile BMI-for-age) has been estimated at 22% (of 2 – 5 year olds) in Alaska [15], 32.6% (of 5 – 8 year olds) in Hawaii [16], 33.5% (of 2-10 year olds) in the Commonwealth of the Northern Mariana Islands [16], 33.7% (of 2 – 5 year olds) in American Samoa [17], and 38.5% (of 5-18 year olds) in Guam, using US CDC reference data [18]. Although these estimates are informative, it is important to note that data are derived from small samples and may not be representative of the population.

Overweight and obese combined (≥85^th^ percentile BMI-for-age) prevalence estimates from NHANES in 2007-2008 [19], among 2-5 year olds, are 21.2% overall and 26.0%, 27.7%, and 27.7% for the minority populations of non-Hispanic black, total Hispanic, and Mexican American children, respectively. Among 6-11 year olds from NHANES in 2007-2008 overweight and obese combined (≥85^th^ percentile BMI-for-age) prevalence estimates are 35.5% overall and 37.6%, 42.6%, and 41.7% for the minority populations of non-Hispanic black, total Hispanic, and Mexican American children, respectively. The 2009-2010 cycle of NHANES documents similarly high prevalence among some US minority groups (Black, Mexican American) [2]. These estimates are similar to the existing estimates from the noncontiguous US states and US Affiliated Pacific Island Jurisdictions. Data from the Supplemental Nutrition Program for Women, Infants and Children (WIC) in 2006 estimate prevalence of combined overweight and obesity (≥85^th^ percentile BMI-for-age) in children ages 2-5 years at 34.7% for Native American/Alaska Native and 33.4% for Native Hawaiian/Pacific Islanders [20]. In contrast, the estimates among the Asian, Black, and White children are 17.9%, 20.8%, and 21.5%, respectively [20].

Despite the serious underrepresentation of the Pacific Region in obesity research, the high prevalence of chronic conditions in the region has prompted the US Affiliated Pacific Islands (AS, CNMI, Guam, FSM, Palau and RMI) to declare a “State of Emergency” [21]. Evidenced by the high proportions of Pacific Island adults who are overweight and obese, prevention of overweight and obesity among children in the Pacific as primary prevention of chronic conditions is of great focus and concern [22].

### Establishment of CHL

The Children’s Healthy Living Program for Remote Underserved Minority Populations in the Pacific Region (CHL) is a partnership among the remote Pacific jurisdictions of Alaska, AS, CNMI, the Freely Associated States of Micronesia (FAS including RMI, Republic of Palau, FSM), Guam, and Hawaii to study child obesity among Pacific children, ages 2-8 years. The program is sponsored by the United States Department of Agriculture (USDA), Agriculture and Food Research Initiative. To address the child obesity epidemic in the Pacific, the CHL partners have identified the following program objectives: 1) Conduct program/data inventories and situational analysis; 2) Train 22 professionals and paraprofessionals in obesity prevention; 3) Develop a Pacific food, nutrition, and physical activity data management and evaluation system; 4) Develop and conduct a community-based environmental intervention to prevent, maintain, or reduce young child overweight and obesity; 5) Evaluate the environmental intervention; and 6) Incur at least one obesity prevention policy change per jurisdiction.

The focus of this paper is on objectives 4-6, which relate specifically to the rationale and design of a community randomized environmental intervention trial in five CHL jurisdictions, and the evaluation of these efforts. Intervention planning involves the modification of three aspects of the environment (social/cultural, physical/built, political/economic) to improve the diet quality and physical activity level of young children (See Figure 1). The methodology and results of program/data inventories and situation analysis, critical to the design of the strategy and content of the community intervention, has been published elsewhere [23].

**Figure 1 F1:**
[figure not shown]
The Children’s Healthy Living Program model to influence multiple aspects of the environment to promote healthy food intake and physical Activity in young children (2 - 8 years) as a method to prevent early childhood obesity in the US Affiliated Pacific.

The investigators hypothesized that children in communities receiving the CHL obesity prevention intervention would differ from their counterparts in communities not receiving the CHL obesity prevention intervention. All successful components of the CHL intervention are planned to be implemented in the comparison communities after the trial is completed (i.e., delayed “optimized” intervention). Specifically, the investigators hypothesized that, relative to children in the comparison communities, children in the intervention group will have the following differences:

1) lower weight and BMI velocities.

2) increased sleep.

3) reduced consumption of sugar-sweetened beverages (SSB).

4) higher fruit and vegetable intake.

5) higher water intake.

6) reduced TV/video viewing.

7) increased physical activity.

8) lower prevalence of acanthosis nigricans (AN).

The CHL intervention targeted the following changes: a reduction in 0.08 of BMI z-score, an addition of 15 min/day of sleep, a reduction of 0.5 cups/day of SSB, an increase of 1 serving/day of fruits and vegetables, an increase of 0.5 cups/day of water, a reduction of 10 min/day of TV/video viewing, and a reduction of 5% in AN. The targets are goals of the intervention and provide guidance for messaging. The differences that the CHL study is powered to detect are provided in the Power and sample size calculations section below.

Previous randomized controlled trial studies in young children, 2-8 years of age, that focused on at least one of CHL’s primary outcomes, showed a positive effect of intervention on body mass index (BMI), food intake, and/or physical activity (PA) [24-29]. Multiple intervention strategies were used in another community trial that were shown to be safe and effective in reducing unhealthy weight gain in children, without increasing health inequalities [30]. That study included efforts to modify children’s food intake and physical activity, and parental involvement with the children around food and physical activity. However, data on PA expenditure and on overall diet quality of participants in these trials are limited. In addition, the populations included in most of these studies are whites in the US, Australia, or Europe. There is little known on the efficacy of such actions in remote diverse populations of Pacific Islander, Native Hawaiian or Alaska Native ethnicity. CHL will be able to fill these gaps in the peer reviewed literature.

## Methods/Design

The CHL Community Randomized Trial is an environmental intervention trial in five jurisdictions: Alaska, AS, CNMI, Guam, and Hawaii. The Freely Associated States of Micronesia, which includes FSM, the Republic of Palau, and RMI, will conduct elements of the CHL sampling framework and measurements to provide prevalence data, but are not engaged in the community intervention trial. The CHL Program was designed to monitor and evaluate the prevalence of obesity in the region through the baseline and follow-up data, while testing the intervention for impact by comparing intervention with non-intervention communities.

The community intervention activities are quantitatively and qualitatively evaluated [31] in Alaska, AS, CNMI, Guam, and Hawaii to determine the impact of the intervention. The intervention was developed through blending findings from a community engagement process that allowed the community to identify and prioritize strategies [23] and review of evidence based literature.

Institutional Review Board approvals from the University of Alaska Fairbanks, University of Guam, and University of Hawai'i at Manoa were attained prior to data collection. The American Samoa Community College and the Northern Marianas College, and the institutional partners in the Freely Associated States of Micronesia ceded their Institutional Review to the University of Hawai'i at Manoa.

In addition, approvals for working with teachers and parents of Head Start (a US federally funded program that educates preschool-age children and their families) and government-sponsored Early Childhood Education programs in the Freely Associated States of Micronesia were received in coordination with the program directors and/or boards, when appropriate. Other local level agreements included approvals from the chiefs (matai) and ministers (faifeau) of participating American Samoan villages and the mayors in participating villages in Guam.

### Site selection process

Communities were identified in Alaska, American Samoa, CNMI, Guam and Hawaii using the 2000 US Census tract data since 2010 data was not available at the census tract level [32] at the time that sites were selected in 2011. In the FAS, 2010 country census data were used to inform selection of sites for prevalence survey data collection [33-35]. Community selection was based on the following eligibility criteria: population size of >1000, >25% of the population of indigenous/native descent (15% in Alaska due to no census tract with a population of more than 1000 having more than 25% indigenous/native), and >10% of the population under age 10 years (based on combining census tract data groups of < 5 years of age and 5 – 9 years of age, in order to have sufficient population size for CHL target of 2 to 8 year olds). Additional selection criteria included having adequate settings for sampling children (e.g., schools); evidence that children live and go to school in the same community (i.e., not a commuter community), ensuring that the measured children have an opportunity to be exposed to the intervention; a minimal risk of contamination between matched-pair communities; having reasonable accessibility for the CHL team (e.g., isolated communities that would require substantial travel logistics were excluded); community cohesiveness [36]; having sufficient settings for intervention (e.g., community centers, parks, churches, and stores); and for the FAS, scheduled air or boat service. A list of all eligible communities was created in each of the jurisdictions based on the above criteria.

Communities in each of the five jurisdictions were selected to participate in the intervention trial. In American Samoa, CNMI, Guam and Hawaii, four communities were selected, while two communities were selected in Alaska due to large distances between sites. The communities were matched to form pairs (1 matched-pair in Alaska and 2 matched-pairs for the other jurisdictions; see Figure 2). The pairs were formed by matching communities on the following factors: percentage in poverty based on U.S. census, population density based on U.S. census, distance from urban centers, and percentage overweight/obesity, when available. In each pair, one community was randomly assigned to intervention and the other to a delayed optimized intervention (community will receive intervention at the end of the main trial).

**Figure 2 F2:**
[figure not shown]
**Children’s Healthy Living Program study design schematic.** *Alaska will only include 4 communities. ^†^Alaska will only include 1 community.

Randomization to intervention, in general, produces study groups that are comparable with respect to confounding variables [37]. An independent statistician performed the randomization.

Two additional non-matched communities (third and fourth for Alaska and fifth and sixth for other jurisdictions) were selected from the eligible list to serve as temporal indicators of anthropometry status (see Figure 2). Generally, the communities selected for temporal assessment had been considered to participate as a matched pair; however, they often did not match another eligible community well or they had less community cohesiveness, which was not as important for a community providing prevalence information only. The temporal communities will not receive the intervention program,

In the FAS region, 3-5 communities were selected for collection of baseline (prevalence) survey data in each of Chuuk, Kosrae, Pohnpei, Yap, Palau and the RMI (n=200 children per location), according to the same criteria, plus a criteria of geographic representation. A total of 27 communities will provide baseline (prevalence) survey data from the FAS.

Thus, in total, four communities in Alaska and six communities in each of the remaining four CHL intervention jurisdictions were selected for a total of twenty-eight communities across the CHL region for participation in the CHL community intervention trial: 9 matched pairs (18 sites total) and 10 temporal sites.

A cross-sectional sample of children in each of the CHL intervention communities is being assessed for outcomes at baseline and at 24 months (18 months post-intervention). Additionally, the outcomes are being assessed in the FAS region to provide prevalence information.

The intervention does not explicitly target the assessed children; they serve as representatives of their communities. Children who participate at both time points provide repeated measures and serve as an embedded longitudinal sample.

### Power and sample size calculations

Sample size estimates were based on the need for a sufficient number of communities and children in each of the five jurisdictions to ensure adequate statistical power to detect meaningful differences between intervention arms in overweight and related outcomes (listed previously) overall and for select outcomes within jurisdictions. The effect size (Cohen’s d) [38] was calculated based on an analysis of 2000 simulated data sets with children clustered within community clustered within jurisdiction. The intervention effect was tested based on an F test of the interaction term of intervention group and time from a mixed model of the outcomes, accounting for the clustering in a group-randomized trial (GRT) by adjusting the test degrees of freedom to the number of communities [39]. The calculations assume a minimum n of 150 children with anthropometry and a minimum n of 100 children with accelerometry and food and activity logs in 6 communities in four jurisdictions and in two communities in Alaska; this assumption is conservative as the goal is a sample size of 180 children per community. An expected correlation for communities within jurisdictions was low with an estimate of the interclass correlation coefficient (ICC) that varied between 0.02 to 0.04. We assumed a critical level of 0.05 (two-sided), a power of 80%, and a constant sample size at baseline and at 24 months. The respective effect sizes for an ICC of 0.02 and 0.04 are modest at 0.26 and 0.35 for outcomes with n=150. Using means and variances for the outcomes from previous research [24,40,41], the minimum detectable differences for the two ICC values were 0.09 and 0.12 for BMI z-score, 21 and 28 minutes of television viewing, and 11 and 15 minutes of sleep. The respective effect sizes for an ICC of 0.02 and 0.04 are also modest at 0.31 and 0.42 for outcomes with n=100. Using means and variances for the outcomes from previous research [24,40,42,43], the minimum detectable differences for the two ICC values were 0.50 and 0.67 servings of vegetables, 0.45 and 0.61 servings of fruits, 0.45 and 0.60 servings of water, 0.34 and 0.46 servings of SSB, and 33 and 45 minutes of PA with metabolic equivalent values (METs) > 3, based on accelerometry.

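### The only named test of the intervention effect, the group-by-time interaction, is valid but less efficient than adjusting for the baseline community mean; the gain depends on a correlation the article does not state

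*Protocol article*

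**What the plan says.** Under Power and sample size calculations, the Protocol article states that the intervention effect was "tested based on an F test of the interaction term of intervention group and time from a mixed model", with clustering handled "by adjusting the test degrees of freedom to the number of communities". No other test of the effect appears, and adjustment for the baseline value of the outcome is not mentioned. The one adjustment factor named is the community readiness score (Community readiness assessment).

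Allocation is by randomisation within matched pairs. Site selection process: "In each pair, one community was randomly assigned to intervention and the other to a delayed optimized intervention". Table 1 shows the individual outcomes measured at 0 and 24 months in all matched-pair communities. The correlation between a community's baseline and 24-month means is not given. Participant recruitment goals plans to remeasure 40-50% of the baseline children; the rest of each wave is a separate sample.

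**The concern.** With two waves and a free baseline difference between arms, the group-by-time interaction is a difference in differences. It subtracts the baseline community mean in full, whether or not that mean predicts the 24-month mean well. Where the correlation is weak, subtraction mostly adds noise. Randomisation makes the expected baseline means equal, so a regression adjustment can use the baseline only as far as it is informative and still target the same effect.

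With nine communities per arm, precision is scarce. The baseline data are being collected anyway, so any gain needs no extra fieldwork.

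**Working it through.** **Inputs.** From Power and sample size calculations: "We assumed a critical level of 0.05 (two-sided), a power of 80%, and a constant sample size at baseline and at 24 months"; 150 children per community for anthropometry; ICC 0.02 and 0.04; detectable effects 0.26 and 0.35. That section counts children "in 6 communities in four jurisdictions and in two communities in Alaska", which is 6 × 4 + 2 = 26 communities. The text following Figure 2 gives "9 matched pairs (18 sites total) and 10 temporal sites", so 18 are randomised. r is not stated and is varied from 0 to 0.7 as an assumption.

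**Formulas**, with g communities per arm and outcome SD 1:
- Variance of one community mean: S = ICC + (1 − ICC)/n. This is 0.02 + 0.98/150 = 0.02653, and 0.04 + 0.96/150 = 0.0464.
- Interaction test: Var = 2(1 − r) × S × 2/g, df = 2g − 2.
- Baseline-adjusted: Var = (1 − r²) × S × 2/g, df = 2g − 3, multiplied by 1 + 1/(2g − 4) for estimating the slope.
- Ratio before the slope cost: 2(1 − r)/(1 − r²) = 2/(1 + r), which is 2.0, 1.48, 1.33 and 1.18 at r = 0, 0.35, 0.5 and 0.7.

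Power is from the noncentral t distribution, two-sided 0.05.

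**The article's own figures first.** With 26 communities and r = 0, the interaction SE is √(2 × 0.02653 × 2/13) = 0.0904 at ICC 0.02 and √(2 × 0.0464 × 2/13) = 0.1195 at ICC 0.04. Detectable effects are 0.264 and 0.349, so 0.26 and 0.35 reproduce. They also reproduce with 18 communities and r = 0.35 (0.261 and 0.346). The n = 100 figures (0.31 and 0.42) fit neither: 26 communities at r = 0 give 0.280 and 0.361, and 18 at r = 0.35 give 0.277 and 0.357. The article's figures therefore do not identify r.

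**Power at d = 0.26/0.35, n = 150, ICC 0.02/0.04**

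| Communities | r | Interaction | Baseline-adjusted | Gain (points) |
|---|---|---|---|---|
| 18 | 0 | 61%/63% | 86%/88% | about 25 |
| 18 | 0.35 | 80%/81% | 90%/91% | 10-11 |
| 18 | 0.5 | 89%/90% | 94%/95% | about 5 |
| 18 | 0.7 | 98%/99% | 99%/99% | under 1 |
| 26 | 0 | 79%/80% | 97%/97% | 17-18 |

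Worked case, 18 communities, ICC 0.02, r = 0: interaction SE = √(2 × 0.02653 × 2/9) = 0.1086; adjusted SE = √(0.02653 × 2/9 × 15/14) = 0.0795. The detectable effect falls from 0.324 to 0.238. At ICC 0.04 it falls from 0.429 to 0.315.

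**Checks.** A 20,000-replicate simulation with 9 against 9 communities at r = 0 gave power 0.614 against 0.863 and 0.630 against 0.878, with null rejection of 0.046 to 0.053 for both methods. Taking df from the nine pairs (8, or 7 after adjustment), with no variance gain credited to matching, lowers both columns but leaves the gap: 56%/57% to 80%/81% at r = 0, and 74%/75% to 85%/86% at r = 0.35.

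**Where adjustment stops helping.** With 18 communities the slope cost is 15/14, so the variances break even when 2/(1 + r) = 15/14, at r = 28/15 − 1 = 0.87. Above that the interaction test is marginally more precise.

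**The case against.** A reader might infer that, on the article's own planning assumptions, the interaction test doubles the variance and throws away about 25 points of power. The document does not support that. A correlation of 0 is back-calculated, and it fits the stated effects only with 26 communities, where the gain is 17-18 points. The 25 points arise by carrying r = 0 over to the 18 randomised communities. The 26-versus-18 discrepancy is a separate error and should not be charged to the choice of test. With 18 communities and r about 0.35 the same stated effects appear, and the gain is about 10 points.

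The document also points towards a positive r: the same communities are surveyed twice, and many children are to be remeasured. If half the community variance persists and all children are new, r = 0.5 × ICC/S, which is 0.38 or 0.43. The interaction test then already exceeds 80% power.

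Three further objections carry less weight.
- The quoted sentence describes the power simulation, and a SAP that is not shown may specify adjustment. That is possible, but this is the only test the article states, and the two should agree.
- Hypotheses and outcomes are framed as velocities and changes. This is no obstacle: with the baseline mean as a covariate, analysing change or the 24-month value gives the same treatment estimate.
- Study design says intervention communities were measured first within a 12-month baseline period, so equal expected baselines are not assured for age- or season-dependent outcomes. This stands as a caveat, but it affects the interaction test too.

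**Conclusion.** The point holds as one of efficiency, not validity: both approaches keep the 5% error rate. For r of 0 or more, the interaction variance exceeds the adjusted variance by a factor of at most 2, and the excess shrinks as r rises. For the 18 randomised communities the gain runs from about 25 points of power at r = 0, through about 10 at r = 0.35 and 5 at r = 0.5, to under 1 at r = 0.7. These figures assume equal arms, 150 children per community at each wave, the stated ICCs and effects, and equal expected baselines. No single value should be quoted as the loss, because r is not stated and the published effect sizes do not determine it. The change is still worth making: it costs little, and it helps most where the interaction test is weakest.

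**What to change.** Name as the primary analysis the between-arm difference at 24 months, adjusted for the community's baseline mean of the same outcome. Equivalently in aim, use a mixed model with a common baseline mean across arms and random community and community-by-time terms. Either form should respect the matched pairs or jurisdictions and take its degrees of freedom from the communities or pairs. Keep the interaction estimate as a sensitivity analysis. State the assumed r and show power over a range of it, using the number of communities actually randomised.

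The cost is analysis wording and about one degree of freedom (16 to 15 without pairing), plus reliance on equal expected baselines. Baseline measurement timing should therefore be compared between arms and its influence examined, for example by adjusting for age and measurement date.

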Abbreviated measures are completed in temporal communities during transition periods between matched-pair communities or after all matched-pair community assessments are completed. The scheduled visits are limited to one visit, which consists of an orientation to the study, informed consent, the completion of a demographic questionnaire, and the collection of the child’s anthropometric measurements. Measurement settings included both school settings and community-based settings. Compensation for participation was provided at the end of visit 1 ($7 in each of Hawaii, American Samoa, and CNMI, $10 in Guam and $25 in Alaska). Community assessments are not conducted in the temporal communities. Additionally, recruitment group leaders (teachers, community leaders) are provided with $20 for their assistance with recruitment groups in all jurisdictions (including the FAS).

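### The power calculation counts 26 communities but only 18 are randomised, so the detectable differences for the n=150 outcomes are too favourable

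*Protocol article*

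**What the plan says.** In the protocol article, Power and sample size calculations bases its simulation on at least 150 children per community for anthropometry and 100 for accelerometry and logs, "in 6 communities in four jurisdictions and in two communities in Alaska; this assumption is conservative". The test is the group-by-time interaction, two-sided 5%, 80% power, with degrees of freedom tied to the number of communities. For ICCs of 0.02 and 0.04 it reports effect sizes of 0.26 and 0.35 at n=150, and 0.31 and 0.42 at n=100. The n=150 values are turned into detectable differences for BMI z-score (0.09 and 0.12), television (21 and 28 minutes) and sleep (11 and 15 minutes).

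Site selection process describes a different number of communities: "In American Samoa, CNMI, Guam and Hawaii, four communities were selected, while two communities were selected in Alaska". It adds: "In each pair, one community was randomly assigned to intervention and the other to a delayed optimized intervention". The text after Figure 2 totals the sites as "9 matched pairs (18 sites total) and 10 temporal sites" and says of the second group: "The temporal communities will not receive the intervention program". Under Study design, "Abbreviated measures are completed in temporal communities", and Table 1 shows only demographics and anthropometry for them.

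**The concern.** Six communities in each of four jurisdictions plus two in Alaska is 26. The randomised design has 18. The article's full list for the five jurisdictions has 28. The figure of 26 is therefore the 18 trial sites plus the two temporal sites in each jurisdiction except Alaska.

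Temporal sites cannot stand in for randomised communities. They are unmatched and untreated, and several were left out of the pairs because they matched poorly or were less cohesive. They also supply no television or sleep data, although the power section treats both as n=150 outcomes.

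In a group-randomised trial the number of communities largely sets the power. The Background refers readers to this section for what the study is powered to detect. If the figures belong to a larger design, a null result could be read as excluding effects that the trial had only a moderate chance of finding.

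**Working it through.** **Inputs.** From Power and sample size calculations: n = 150 or 100 children per community per time point, ICC 0.02 or 0.04, two-sided alpha 0.05, power 80%, equal samples at both times. From Site selection process: 9 pairs allocated 1:1, so 9 communities per arm. A count of 26 split equally gives 13 per arm. Two inputs are assumptions, because the article does not state them: degrees of freedom (df) = communities − 2, and no correlation of a community's effect between baseline and 24 months.

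**Formula.** In SD units, with k communities per arm, the group-by-time contrast of community means has

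SE = √[2 × (ICC + (1 − ICC)/n) × (2/k)].

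Power comes from the non-central t distribution.

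**Step 1: reproduce the stated n=150 figures with 26 communities (k = 13, df 24).**
- ICC 0.02: 0.02 + 0.98/150 = 0.02653, SE = 0.0904, detectable d = 0.264 (stated 0.26).
- ICC 0.04: 0.04 + 0.96/150 = 0.0464, SE = 0.1195, detectable d = 0.349 (stated 0.35).
- Power at the stated effects is 78.8% and 80.2%, so the figures reproduce.

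**Step 2: use the 18 randomised communities (k = 9, df 16).**
- ICC 0.02: SE = 0.1086, detectable d = 0.324, power at 0.26 = 61.4%.
- ICC 0.04: SE = 0.1436, detectable d = 0.429, power at 0.35 = 62.9%.

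**Step 3: vary the assumptions (18 communities, n=150).**

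| Assumption | Power at 0.26 (ICC 0.02) | Power at 0.35 (ICC 0.04) |
|---|---|---|
| df 8 (paired) | 55.7% | 57.2% |
| df 12 | 59.5% | 61.0% |
| df 16 | 61.4% | 62.9% |
| df 32 | 64.1% | 65.7% |
| normal approximation | 66.8% | 68.3% |
| df 16, over-time correlation 0.2 | 68.4% | 71.1% |
| df 16, over-time correlation 0.4 | 76.7% | 80.7% |
| df 16, over-time correlation 0.5 | 81.2% | 85.8% |
| df 16, n = 180, no correlation | 63.2% | 63.9% |

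**Step 4: restate the n=150 differences.** The implied SD is the stated difference divided by the stated d; multiply it by 0.324 or 0.429.
- BMI z-score: 0.09/0.26 = 0.346 and 0.12/0.35 = 0.343, giving about 0.11 and 0.15.
- Television: 21/0.26 = 80.8 and 28/0.35 = 80, giving about 26 and 34 to 35 minutes.
- Sleep: 11/0.26 = 42.3 and 15/0.35 = 42.9, giving about 14 and 18 minutes.

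**Step 5: the n=100 figures.** The same model gives 0.280 and 0.361 with 26 communities, and 0.343 and 0.443 with 18. The stated 0.31 and 0.42 match neither. With 18 communities, power at the stated values is about 72% and 76%.

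**The case against.** Four points can be made for the plan.

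- **The n=100 outcomes.** A reader might infer that every detectable difference was computed on 26 communities and is too favourable for that reason. The document does not support this. Against 26 communities the n=100 effect sizes are pessimistic, and they lie nearer to the values for 18: a normal approximation with 18 gives 0.322 and 0.416. They also equal the n=150 values times √(26/18), since 0.26 × 1.202 = 0.312 and 0.35 × 1.202 = 0.421. That is suggestive only, but the diet and activity figures may rest on about the right number of communities. The demonstrated error covers BMI z-score, television and sleep.

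- **Correlation over time.** The same communities are measured twice, and Participant recruitment goals aims to remeasure 40-50% of children, so some correlation is plausible. At 0.4, 18 communities give detectable effects of 0.271 and 0.347, close to the stated pair. This stands as a limit on the size of the loss. It does not explain the figures: the article states no correlation, its text gives the larger count, and a correlation of 0.4 gives 0.294 and 0.365 at n=100, not 0.31 and 0.42.

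- **The claim of conservatism.** It refers to planning on 150 children when the goal is 180. In that sense it is correct and need not be deleted. But Step 3 shows that the margin adds only 1 to 2 points of power, so it does not offset eight missing communities.

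- **Temporal sites as extra controls.** With 9 against 17 communities (df 24), power at the stated effects is 74.8% and 76.2%. This would be possible for anthropometry only and would make the comparison partly non-randomised.

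**Conclusion.** The point holds for the n=150 outcomes. The mismatch of 26 against 18 follows from the text and needs no model. The reproduction in Step 1 indicates that the larger count entered the calculation and is not just a slip of wording.

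The size is conditional. With uncorrelated community effects and df 16, power at the stated effects is about 61% and 63%, or about 56% to 68% across df choices. It is higher if community effects correlate over time. A reader should therefore not take 61-63% as the trial's established power.

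The basis of the n=100 effect sizes is unclear. They are not shown to rest on 26 communities, and the values of 0.343 and 0.443 should not be adopted as replacements, because the model behind them does not reproduce the article's own n=100 figures. Nothing here faults the randomisation, the measurements or the planned test. What is wrong is the stated power and the detectable differences derived from it.

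**What to change.** - Rerun the existing simulation with the 18 randomised communities, for both n=150 and n=100.
- State the degrees of freedom and the over-time correlation of community effects that it assumes.
- Restate the effect sizes, detectable differences or power from that rerun. The figures above indicate the likely size and are not replacement text.
- State that temporal communities are excluded from the intervention-versus-comparison test.
- Limit the word conservative to children per community (150 against a goal of 180), and note that this does not make up for the smaller number of communities.

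The cost is one rerun and revised wording. No extra communities or children are needed; the only downside is less favourable stated figures.
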